## Abstract

**Background:**

Several studies have demonstrated an association between psychological risk factors and HIV disease progression. However, there is limited information on the use of psychological interventions to improve HIV treatment outcomes in young people living with HIV.

**Objective:**

This pilot trial aims to evaluate the feasibility, acceptability and preliminary effectiveness of group support psychotherapy in improving adherence to anti-retroviral therapy and viral suppression in young people living with HIV in Uganda.

**Methods:**

We recruited 120 young people with HIV, aged 10–18 years, who had non-viral suppression 6 months after initiating first-line anti-retroviral therapy (ART) from community based HIV clinics in Kitgum district, northern Uganda. Participants were randomly assigned to receive GSP plus IAC (*N* = 60) or IAC alone (*N* = 60). Primary outcomes will be indicators of feasibility and acceptability as well as preliminary effectiveness of GSP in improving ART adherence and viral suppression analysed by intention to treat using cluster-adjusted t tests and permutation tests. Secondary outcomes will be measures of depression, anxiety and cost-effectiveness.

**Results:**

The trial has been approved by the Makerere College of Health Sciences School of Health Sciences Research Ethics Committee, and the Uganda National Council of Science and Technology. Recruitment began in June 2021 and 120 young people living with HIV with their adult caregivers have been recruited to the trial. An analysis of baseline and 6-month data is in progress. The results of this trial will not only be presented at national and international conferences but also submitted for publication in peer-reviewed journals and as a report to the funding agencies.

**Conclusions:**

This pilot trial will provide critical evidence to support the ongoing mental health integration into routine HIV care in Uganda.

**Trial Registration:**

Pan African Clinical Trials Registry (PACTR): 202006601935462

## Introduction

The availability of anti-retroviral therapy (ART) has improved the life expectancy of persons living with HIV worldwide (1). However, a major concern is that, HIV morbidity and mortality have improved drastically among adults, which is not the case among young people (2). Research has shown that young people tend to experience worse immunological and viral suppression outcomes compared to adults (3–6), which in turn contributes to their higher morbidity and mortality (7).

Barriers to successful care of youth with HIV include mental health disorders, poor medication adherence, socioeconomic instability, and HIV-related stigma (8). Also transition of care from pediatric to adult clinics has been described as a challenging period in which the young people have to deal with anxieties, excessive anger, and lack of social support, self-esteem and self-efficacy (9). Consequently, they are prone to poor linkage to care, attrition from care and treatment (10).

In Uganda, the national HIV treatment guidelines include psychosocial support services in the HIV care package (11). However, the nature of psychosocial support is not structured and may not target common psychosocial challenges such as stigma, depression or post-traumatic stress. Enhanced or Intensive adherence counseling has long been used to mitigate non-viral suppression; however, recent findings from Ugandan studies indicate that this strategy may not be sufficient (12, 13).

A retrospective cohort study on all children aged 9 months to 19 years that had been enrolled into 15 HIV care programs in 15 districts supported by the Infectious Diseases Institute (IDI) assessed the outcome of Intensive adherence counseling among 449 children with viral non-suppression (13). A repeat viral load test performed on 274 children who had completed three IAC sessions indicated that 212/274 (77%) were unsuppressed and 62 (23%) were suppressed. There was no report of any other specific psycho-social intervention provided to children with viral non-suppression in the above mentioned 15 HIV care programs.

Researchers call for an urgent need for innovative strategies to respond effectively to the social, emotional and economic challenges faced by young people living with HIV (14). In particular, they recommend for intensified targeted adherence support in order to improve HIV treatment outcomes (15). To this end, a few studies on interventions to promote ART adherence among young people have started to emerge (16–19).

To mitigate mental health challenges and improve HIV treatment outcomes, we developed group support psychotherapy—a culturally sensitive evidence based intervention that has been shown to effectively treat mild to moderate depression, improve posttraumatic stress symptoms, and hazardous alcohol use among adults living with HIV in Uganda (20). Further, exposure to GSP was observed to improve viral load suppression through sequential reduction in depression and improvement in ART adherence among adults living with HIV in Uganda (21).

The cognitive behavioral theory is one of the potential existing theoretical models that could guide the development of mental health interventions for young people living with HIV. Cognitive-behavioral therapy (CBT) is recommended for treatment of children and adolescents (22). We chose to adapt group support psychotherapy for young people because it is based on the principles of cognitive behavior theory, social learning theory, and the sustainable livelihoods framework. The cognitive behavior theory holds that the way we think about our reality is central to how we react to that reality (23). The social learning theory stems from the idea that behavior is learned from the environment by observation, in which the person being observed is referred to as the model (24) The sustainable livelihoods framework shows that the absence of livelihood strategies such as the ability to adapt to adverse situations, network and increase social connections, or work and obtain savings, housing, or land, constrains livelihood opportunities (25).

Given the evidence we have gathered for group support psychotherapy, it can address the complex and dynamic interactions between young people, their families, and their environmental context (26).

The goal of this paper is to describe the protocol for the evaluation of the feasibility, acceptability and preliminary effectiveness of group support psychotherapy in improving ART adherence and viral suppression among HIV positive young people in Uganda. In the preparatory phase of this trial, we aim to conduct community-based participatory qualitative research to obtain information on the potential usefulness of group support psychotherapy in addressing the psychosocial challenges that impact adherence to anti-retroviral therapy and viral suppression among young people with HIV in northern Uganda.

In the trial phase of this study, the primary objective will be to assess the feasibility, acceptability and preliminary effectiveness of GSP in promoting ART adherence and viral suppression among HIV positive young people with non-viral suppression 6 months after initiating first-line ART at community-based HIV clinics in Kitgum district. Secondary objectives will include exploration of indicators of causal mediating processes and contextual influences, exploration of whether or not improvement in psychosocial challenges including depression, posttraumatic stress symptoms, suicide risk, social support, and stigma mediate or modify the effect of GSP on ART adherence and viral suppression, exploration of whether or not promotion of adherence through group support psychotherapy translates into better viral load suppression compared to standard care with intensive adherence counseling (IAC) and exploration of the cost-effectiveness of GSP to improve viral load suppression among HIV positive young people taking anti-retroviral therapy.

We hypothesize that in comparison to the control intervention, GSP will demonstrate better feasibility, acceptability and better preliminary HIV treatment outcomes and better cost-effectiveness. The primary end point will be 6 months after the end of the intervention. Data will be used to design a definitive cluster randomized trial which will test the hypothesis that group support psychotherapy promotes better ART adherence and viral suppression than standard care with intensive adherence counseling among HIV positive young people with non-viral suppression 6 months after initiation of first-line ART in Uganda.

## Methods

### Study setting

Study participants will be recruited from community based HIV clinics in Kitgum district. The clinics take care of approximately 500 young people aged 18 years and below living with HIV. At the time we conceptualized this study, HIV clinic registers in Kitgum district showed that 60% of young people living with HIV (PLWH) initiated on ART were not suppressing the HIV virus. Therefore, we drew our study sample from a pool of approximately 300 young PLWH who had viral non-suppression. Kitgum district has a population of 232,000 individuals with over 90% engaged in small scale agriculture and animal husbandry as their major income generating activity. Kitgum district endured a brutal civil war for two decades (1987–2007) which led to a breakdown of health care delivery systems, loss of property and infrastructure.

### Study design

In the preparatory phase, we shall conduct a qualitative study. Thirty dyads of young people with non-viral suppression and their caregivers will be exposed to 8 sessions of the current group support psychotherapy intervention (GSP). At the end of the intervention, 6 focus group discussions will be conducted with the young people (*N* = 2); their caregivers (*N* = 2) and their HIV care providers (*N* = 2). Key informant interviews will be held with various stakeholders including psychologists, pediatricians, child and adolescent psychiatrists, district health officials, community leaders and religious leaders to determine their perceptions towards using GSP as an intervention to promote adherence to ART alongside Intensive Adherence Counseling (IAC) among young people with HIV and their caregivers. The main objective of the workshops will be to discuss the potential of the current GSP intervention content, in addressing possible challenges/barriers associated with adherence to ART among young people with HIV. A community advisory board will be created to maintain the community's trust in the research process and members will also participate in key informant interviews.

Data from these KIs/FGDs will be used to modify intervention content/delivery. Purposive sampling will be used for the qualitative interviews, which will be conducted in the local language, audio-taped and transcribed and translated (where required) verbatim. Informed consent will be obtained from participants before conducting KIs/FGDs. Thereafter, consultative meetings will be held with child and adolescent HIV and mental health experts to review our theoretical framework and assemble treatment strategies to be used in the GSP model for young people with HIV.

In the trial phase, we shall conduct a pilot single-blinded randomized controlled trial to test the feasibility and acceptability of using GSP in combination with standard care IAC vs. standard care IAC only to promote ART adherence and improve viral suppression among HIV positive young people with non-virological suppression 6 months after initiation of first-line ART (see Consolidated Standards of Reporting Trials diagram in Figure 1). We aim to randomize 120 youth/caregiver dyads (1:1) to either both GSP and IAC or IAC only. Participants will be evaluated at baseline, at the end of treatment, 6 and 12 months after treatment. A longitudinal process evaluation of the delivery of GSP-IAC by trained LHWs using mixed methods will run alongside the trial to assess fidelity, and how intervention recipients respond to the different intervention components.

**Figure 1 F1:**
[figure not shown]
Trial flowchart.

The study protocol was registered in the Pan African Clinical Trials Registry. The study was submitted to both the Makerere University School of Health Sciences Research Ethics Committee and the Uganda National Council of Science and Technology. All study participants will be required to provide written informed consent. All study participants will receive a financial incentive to defray transport costs. The reporting of the trial will be in accordance with the Standard Protocol Items: Recommendations for Interventional Trials (SPIRIT) guidelines (27) for intervention trials (see Supplementary Multimedia Appendix S1) and the CONSORT statements for pilot randomized trials (28).

#### Participant eligibility criteria, recruitment, and masking

To be eligible for the study, participant dyads must consist of an HIV sero-positive young person (10–18 years) with ≥1,000 viral copies/ml 6 months after initiating first-line ART and a caregiver aged 19 years and older. Participant dyads will be excluded if they have visual or hearing impairments, active untreated major mental illness (untreated psychosis or mania or high suicide risk) or severe medical conditions (active tuberculosis or pneumonia) that would interfere with participation in interventions.

All participants will be recruited from community-based HIV clinics in Kitgum district. Potential participants will be identified by their HIV care providers as not responding to their current antiretroviral (ARV) treatment regimen (defined per local clinic standards as viral load >1,000 copies/ml). Research assistants (RAs) and other study staff situated at the HIV clinic will work with staff in the HIV clinics to identify potential participants as they wait for their medication refills. RAs will be Luo-speaking staff with GSP research and HIV clinical experience. They will be extensively trained in the study protocol and supervised weekly by the project coordinator who is a social worker. They will be screened for psychosis and mania using quick screening questions for psychotic and manic symptoms. They will also be screened for high suicide risk using the SAD PERSONS scale. Individuals with psychotic and/or manic symptoms and /or high suicide risk will be excluded from the study.

All young people (10–18 years)/caregiver dyads eligible to participate in the study will be approached by research assistants who will explain study procedures, determine eligibility, and then obtain informed assent/consent. Each dyad which assents/consents will be assigned to receive baseline interviewer administered demographic and psychosocial assessment battery and thereafter randomly assigned to receive either both GSP and IAC or IAC only.

#### Randomisation and masking

Randomisation will be done by urn randomisation picked by each participant. The young males and females will be separated into two groups. Each group will be presented with pieces of paper in opaque envelopes whereby half the number of papers will be marked X and the other half Y. Each member of the group will be asked to each pick one envelope. Individuals who pick papers with X will be assigned to both GSP and IAC while those who picked papers with Y will be assigned to IAC only. The same process was repeated for the caregivers.

By design, both experimental and control interventions will be identifiable to participants but will be masked to independent outcome assessors, and data analysts.

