#### Participant safety

During baseline assessments, participants will be carefully screened and individuals for whom the interventions are deemed medically inappropriate or unsafe will be excluded as described in the exclusion criteria. Independent outcome assessors will screen all participants for adverse events at the end of treatment and at 6 months after the end of the intervention using a standard interview and reporting form.

Any unfavorable and unintended sign or symptom associated with the participation in group support psychotherapy, regardless of whether it is considered related to the therapy will be regarded as an adverse event (AE).Any AE that results in any of the following outcomes: Death, Life-threatening, Event requiring inpatient hospitalization, Persistent or significant disability/incapacity will be regarded as a serious adverse event (SAE). Expected AEs associated with this study would be suicide attempts due to lack of treatment response to the group support psychotherapy.

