**Primary outcomes**					
Indicators of feasibility	The proportion of eligible participants who take up either intervention (**Reach**) The proportion who attended all 8 sessions of either intervention (**Dose delivered**) The proportion who are lost to follow-up (**Attrition**) will be determined from the attendance registers		✓		
Indicators of acceptability	A 9-item questionnaire (34) will assess participant's satisfaction, the group facilitators’ knowledge and attitudes, and the participant evaluation of the intervention's ability to reduce stress		✓		
Adherence to ART	One question “During the past three weeks, on how many days have you missed taking all your medication doses?”	✓		✓	✓
Viral Load	Medical charts of study participants	✓		✓	✓

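### The claim of masked assessors and analysts is not reconciled with an adverse-event definition worded only for GSP, or with attendance data likely to reveal the arm

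*Protocol article*

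**What the plan says.** Under Study design the trial is labelled single-blind ("we shall conduct a pilot single-blinded randomized controlled trial"). Randomisation and masking explains the label: participants can tell which intervention they receive, but the interventions "will be masked to independent outcome assessors, and data analysts".

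Participant safety gives the harms screen to the same named role: "Independent outcome assessors will screen all participants for adverse events at the end of treatment and at 6 months after the end of the intervention". One common interview and form serves everyone; no arm-specific version is described. The section then defines the event to be found: "Any unfavorable and unintended sign or symptom associated with the participation in group support psychotherapy, regardless of whether it is considered related to the therapy" counts as an adverse event. The one expected event it names is a suicide attempt attributed to GSP not working. No parallel definition is given for IAC alone.

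Table 2 makes dose delivered a feasibility outcome, counted as attendance at all of 8 sessions, whichever intervention was received. Its acceptability questionnaire, at month 2, covers the group facilitators' "knowledge and attitudes, and the participant evaluation" of whether the intervention reduces stress. The Quantitative data section compares people who completed every session with those who did not, and collapses 120 participants into 12 groups before comparing arms.

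**The concern.** Participants know their arm. Adherence, a primary outcome, is one self-report question about missed days, and the symptom scales are questionnaires or, for post-traumatic stress, a clinician-administered instrument. For these measures, masking of assessors and analysts is the only safeguard against bias that the article states. If an assessor learns the arm through the harms interview, later questioning and scoring can drift towards the expected result. If the analyst can see the arm, choices made while the analysis is built are no longer protected.

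The same wording has a second consequence. A definition that only a GSP participant can meet gives the IAC-only arm no adverse events to count, so the two arms' harms cannot be compared, although everyone is screened.

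**Working it through.** The plan gives no figure for masking to reproduce, and 60 per arm is a rule-of-thumb choice. The check sets the sections side by side.

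**1. Can the three safety and masking statements hold together?**
- (a) Assessors do not know the arm (Randomisation and masking).
- (b) The same role screens all participants in both arms (Participant safety).
- (c) An event is a sign or symptom tied to taking part in GSP (Participant safety).

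Take an IAC-only participant who reports a symptom. To apply (c), the assessor must know that this person was not in GSP, so (a) gives way. If the assessor records every symptom regardless, (a) survives, but (c) is not the definition in use. If someone holding the allocation applies (c) later, (a) survives, but the IAC-only arm has no adverse events by construction and the screening in (b) yields nothing comparable. The clause on relatedness within (c) removes the judgement of cause; it does not remove the condition of having taken part in GSP.

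**2. When does the harms interview fall relative to the outcomes?** From Table 2 and Participant safety:
- Harms interview: end of treatment (month 2), and 6 months after the intervention.
- Acceptability questionnaire: month 2.
- Symptom, suicide-risk, support and stigma scales: baseline, 2, 6 and 12 months.
- Adherence question: baseline, 6 and 12 months.

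The first harms interview therefore coincides with the first post-baseline symptom scales and precedes every post-baseline adherence question. Anything an assessor learns at month 2 can carry forward if the same people return.

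**3. Do attendance data reveal the arm?**
- GSP: 8 sessions (GSP section).
- IAC: four or more in the text of the Standard of Care section; three with a conditional fourth in Table 1. These two descriptions also need reconciling.
- The experimental arm receives both. On the Table 1 counts its total is 8 + 3 = 11 or 8 + 4 = 12 sessions, against 3 or 4 in the control arm.

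Raw counts would separate the arms almost completely, whatever the labels. A yes/no flag depends on its definition. With 8 sessions required in either arm, as Table 2 has it, a "yes" points to GSP unless IAC ran to eight. If completion is defined against each arm's own schedule, the flag alone reveals nothing.

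**4. Do group codes reveal the arm?** 120 / 12 = 10 per group, and 60 / 10 = 6 groups per arm. This matches 2 sexes × 3 age bands = 6 GSP groups. Since the plan groups both arms, group codes alone do not identify GSP, and the point does not rest on them.

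**5. Which outcomes are exposed?** The adherence question and the scales. Viral load comes from medical charts and is hardly touched.

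**The case against.** A single standard interview given to everyone does not oblige the assessor to know the arm, and events can be assigned to GSP afterwards by someone holding the allocation. That stands as far as it goes: unmasking is not proven. It does not rescue the definition, which still gives the IAC-only arm nothing to count.

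The article does not say that the people who run the harms interview also give the follow-up scales, or who hands out the acceptability questionnaire. This also stands. The shared role name makes the first the natural reading, no more.

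On the analyst side, a reader might infer that the analysis file shows who had GSP, or that the printed meaning of X and Y unmasks the data. The documents do not support either. No file is described, nothing says that the dataset uses those letters, and attendance could be held apart from a coded efficacy file. What remains is that attendance is part of the planned analysis and differs by design.

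Participants know their arm, so their own reporting bias in adherence survives even perfect assessor masking, and the fix does not remove it. This limits the gain but does not make the stated safeguard worthless.

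Form order and program locking are details that an article may leave to a fuller document. Agreed, and their absence is not the finding. The finding is that two sections of the article conflict as worded.

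**Conclusion.** The point holds as an unreconciled conflict that should be corrected. The masking statement and the GSP-only adverse-event definition cannot both be applied literally to both arms. Assessor masking is put at risk, and harms have no common definition across arms. Analyst masking is at risk because attendance differs by design.

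A reader might go further and conclude that masking fails, or that a particular rise in the false-positive rate follows. The text shows neither. Any such rate would need an assumed scoring shift and an assumed intra-cluster correlation, and the article gives no value for either. The size of the bias is therefore left unstated.

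The assessor part assumes that the shared role name means shared staff. The analyst part assumes that session data reach the analyst in a form that reflects the different schedules. The effect is confined to self-reported and assessor-collected outcomes. Confidence is moderate.

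**What to change.** - Reconcile Randomisation and masking with Participant safety: define an adverse event as any unfavourable sign or symptom during study participation in either arm, with no reference to GSP, and word the expected event in the same neutral way. This protects later visits and allows harms to be compared.
- At each visit, complete the outcome measures before the adverse-event interview and the acceptability questionnaire. Order protects only the visit at which it is applied, so it supplements the neutral wording.
- Write and lock the efficacy program on shuffled arm and group codes before attendance data are released, then run it on the true codes. Otherwise withdraw the claim that analysts are masked.

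Trial status reports that recruitment closed in October 2021 and that baseline, 6-month and 12-month data are being analysed, so the visit order can no longer be changed here. For this trial, apply the analyst step where it is still possible and report the limit on assessor masking. Carry the definition and the form order into the planned definitive trial. The cost is a small data-handling step and, in the later trial, a changed form order.
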